### Economic analysis

The economic analysis will be conducted from the perspective of the Australian healthcare system and the individual patient, with data collected in a survey every four weeks from the end of the four-week intervention period to the 24-week follow-up assessment. Participants will record all out-of-pocket expenses incurred due to the fractured ankle, including the frequency and costs associated with physiotherapy, other health and hospital services, and the costs of medication. Figure 4 indicates the type of resources which will be captured, the sources of data, and proposed methods of valuation. At the four-week follow-up assessment, participants will also be asked to provide socio-demographic information such as their usual main activity, normal annual household income, the type of private health insurance they have (if any), and whether they are renting, boarding or owners of their homes.

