In this pragmatic trial, participants will be seen at a frequency typical to that which occurs in the clinical setting. Participants in the treatment group will receive two treatment sessions per week for four weeks for joint mobilisation and progression of the exercise programme. Participants allocated to the control group will receive two treatment sessions in the first week, then one session per week for three weeks. In the first session, participants in the control group will be taught the exercises, which will be monitored and progressed in subsequent sessions.

In addition, at the treatment sessions all participants will receive gait retraining, progression of walking aids, and advice on prognosis and return to activities. If required, participants will receive ice for pain relief, and compression and elevation for the management of swelling. No other physiotherapy treatments will be administered during the four-week intervention period.

After each initial treatment session, the treating physiotherapist will receive a phone call from an investigator unblinded to group allocation. Implementation of the experimental protocol for each participant will be discussed to ensure compliance.

At the end of the intervention period, passive joint mobilisation treatment will cease and participants will be allowed to be progressed to exercises other than those in the standardised set. Ankle taping can be performed to assist return to sports.

The timing of discharge will not be dictated in the protocol. Participants will be discharged by their physiotherapists when they return to their previous level of function, reach a plateau in their progress, or choose to discontinue treatment.

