Satisfaction with physiotherapy treatment will be measured at the four-week follow-up assessment on a 100-mm visual analogue scale marked "completely unsatisfactory" at one end and "best possible" at the other. At all follow-up assessments, participants will be asked if the physiotherapy treatment has had any negative effects and, if so, the nature of the effects. They will also record whether they have had treatment other than physiotherapy for the fractured ankle.

The treating physiotherapist will complete a survey for every participant at each follow-up assessment until discharge. Information gathered on this survey will be: the date and reason of discharge (if applicable), number of physiotherapy sessions scheduled, number of physiotherapy sessions attended, exercises prescribed and repetitions completed, any other physiotherapy treatment administered, and, for the treatment group only, the dates, number of sets and duration of the joint mobilisation treatment. This information will be analysed to obtain the length of physiotherapy required, percentage of scheduled sessions attended, compliance of participants to the exercise programme, and compliance of physiotherapists to the experimental protocol.

Data will be collected on paper forms and manually entered into a computer programme. Several strategies will be implemented to ensure the accuracy of the data. Data collection forms will be checked for completion. Data entry will be performed twice and the two entries will be compared to check for errors. Range checks will be performed on outcome values at the completion of data entry.

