### Statistical analysis

Data analysis will be undertaken at the completion of data acquisition and will be by intention to treat (that is, participants will be analysed according to group allocation regardless of compliance) [60]. Missing data will be replaced by the last known value carried forward. The statistician will be given coded data to ensure blinding.

Separate analyses will be performed on the four, 12 and 24 week data, with the four-week (i.e., the end of the intervention period) follow-up being the primary time point for analysis. To test the effects of treatment, between-group differences will be examined with analysis of covariance using a regression approach. The emphasis will be on estimation, but hypothesis tests will also be conducted (alpha = 0.05). Pre-test scores will be entered into the model as the only covariate.

In a secondary analysis designed to test the influence of fracture severity on treatment effects, additional terms (fracture severity, group by fracture severity interaction) will be entered into the regression model. Fracture severity will be categorised into two levels based on the number of malleoli involved: less severe (unimalleolar fractures) and more severe (bimalleolar or trimalleolar fractures). The effect of fracture severity on treatment will be determined by examining the interactions between group of allocation and fracture severity.

Ninety participants (45 per group) will participate in the trial. This sample size provides a 90% probability of detecting a difference between group means of 10 points on the Lower Extremity Functional Scale, assuming a standard deviation of 12 based on a recently published study [41]. These calculations assume a correlation of 0.6 between pre- and post-test measures and an alpha of 0.05, and allowed for 10% dropouts and 20% non-compliance.

The economic evaluation will consist of cost-effectiveness and cost-utility analyses. The cost-effectiveness analysis will use the Lower Extremity Functional Scale as a measure of effectiveness. The cost-utility analysis will use the Assessment of Quality of Life as a measure of utility [43]. The analyses will examine differences between treatment and control participants in terms of costs incurred and reductions in perceived disability (cost-effectiveness analysis) or utility gained (cost-utility analysis).

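### Last value carried forward, the only missing-data rule stated, does not suit four-weekly costs, and the bias it puts into the incremental cost has no fixed direction

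*Protocol article*

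**What the plan says.** The Economic analysis section of the protocol article describes "data collected in a survey every four weeks from the end of the four-week intervention period to the 24-week follow-up assessment". On these surveys, "Participants will record all out-of-pocket expenses incurred due to the fractured ankle". No cost survey at baseline is mentioned. The article does not say whether the first survey looks back over weeks 0 to 4.

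The Statistical analysis section gives one rule for incomplete data: "Missing data will be replaced by the last known value carried forward". It names no exception. The same section sets out the cost-effectiveness and cost-utility analyses and gives no separate rule for costs. The ICER numerator is the difference in average cost between arms. Whether costs would be carried per period or as a running total is not stated.

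Two other parts of the Methods bear on the point. Under Outcome assessment, "The treating physiotherapist will complete a survey for every participant at each follow-up assessment until discharge"; this form records sessions scheduled and attended. Under Interventions, "Participants in the treatment group will receive two treatment sessions per week for four weeks", while the control group "will receive two treatment sessions in the first week, then one session per week for three weeks". Mobilisation stops at the end of week 4.

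**The concern.** A functional score is a state seen at a visit, so carrying it forward at least yields a quantity of the right kind. A four-weekly cost is a flow, and the quantity of interest is its sum over 24 weeks. There are two ways to carry it forward, and neither estimates later spending:

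- **Per period:** the last four weeks' spending is entered again for every later period, although scheduled treatment ends at week 4 and participants are discharged as they recover.
- **Running total:** nothing is added after dropout, so later spending is taken as zero.

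A participant lost before the first survey has no earlier self-reported cost, so the rule supplies no value for that component.

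The result feeds directly into the ICER numerator, and cost-effectiveness is part of the stated primary aim.

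**Working it through.** The article gives no figure for cost or for missing cost data, so there is none to reproduce. The check is an illustration with physiotherapy sessions as the cost unit.

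**Inputs from the article**
- Treatment arm, weeks 0 to 4: 2 × 4 = 8 sessions.
- Control arm, weeks 0 to 4: 2 + 1 + 1 + 1 = 5 sessions.
- Dropout: 10%, borrowed from the sample-size statement ("allowed for 10% dropouts and 20% non-compliance").

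**Assumptions, not in the article**
- Cost is proportional to sessions.
- The first survey is at week 4 and covers weeks 0 to 4, which gives six four-week periods.
- Both arms use p = 1 session in each of the five later periods.
- Dropouts have the same true use as completers.

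**Complete data.** Treatment 8 + 5 = 13, control 5 + 5 = 10, true difference 3.0.

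**Formula.** With a fraction d lost, the arm mean is (1 − d) × complete total + d × filled-in total. For loss just after week 4, the filled-in total is 6 × 8 = 48 (treatment) or 6 × 5 = 30 (control) if carried per period, and 8 or 5 if carried as a running total.

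| Scenario | Treatment | Control | Difference |
|---|---|---|---|
| 10% lost before week 4, scored zero | 0.9×13 = 11.7 | 0.9×10 = 9.0 | 2.7 |
| 10% lost just after week 4, per period | 11.7 + 4.8 = 16.5 | 9.0 + 3.0 = 12.0 | 4.5 |
| 10% lost after week 8 or later, per period | 13.0 | 10.0 | 3.0 |
| 10% lost just after week 4, running total | 11.7 + 0.8 = 12.5 | 9.0 + 0.5 = 9.5 | 3.0 |
| 5% treatment, 15% control lost just after week 4, per period | 12.35 + 2.4 = 14.75 | 8.5 + 4.5 = 13.0 | 1.75 |
| 15% treatment, 5% control lost just after week 4, per period | 11.05 + 7.2 = 18.25 | 9.5 + 1.5 = 11.0 | 7.25 |

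**Uniform loss.** Spread 10% equally over the six intervals, with those lost before week 4 scored zero:
- Per period: (2.7 + 4.5 + 4 × 3.0)/6 = 3.2, which is +7%.
- Running total: (2.7 + 5 × 3.0)/6 = 2.95.

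**Dependence on the assumptions.** With equal dropout just after week 4 and per-period carrying, the difference is 3(1 − d) + 18d = 3 + 15d, whatever the value of p: 3.75 at 5%, 4.5 at 10% and 6.0 at 20%. With unequal dropout (a in treatment, b in control) it is 3 + a(40 − 5p) − b(25 − 5p). At a = 0.05 and b = 0.15 this gives 1.25, 1.75 and 2.25 for p = 0, 1 and 2. If the surveys record only spending after week 4, no survey value contains intervention-period cost and the route to 4.5 disappears.

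**The case against.** A reader might infer that dropouts' costs cannot be scored at all, and that the rule inflates the cost difference against mobilisation by about half. The documents do not support either inference.

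- **Scoring.** The treating physiotherapist's form records sessions attended, so early dropouts need not lack a session count. Only participant-reported costs have no earlier value.
- **Direction and size.** The 4.5 needs several things together: per-period carrying, a first survey covering weeks 0 to 4, all loss just after it, equal dropout in the two arms, and cost proportional to sessions. Anyone lost after week 8 carries a post-intervention period. The article does not say that participants pay per session. The 10% is an allowance in the power calculation for the Lower Extremity Functional Scale, whose primary time point is week 4; it is not a forecast of later loss.
- **Scope.** The carry-forward sentence stands just before the 4-, 12- and 24-week covariance analyses and may have been meant for clinical outcomes only. Figure 4 is not shown, and an article may leave cost handling to a fuller document. The primary conclusions rest on four-week data, and a sensitivity analysis of costs is planned.

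The first two objections stand and limit the claim. The third stands only in part. The article does fix a rule, without restriction, in the section that contains the economic evaluation, so the point concerns an unsuitable stated rule and not absent detail. Figure 4 is described as covering resources, sources and valuation, not missing data. The sensitivity analysis varies costs by literature values and by the bounds of the trial's own results; it names no alternative missing-data method, and those bounds would themselves rest on the filled-in data.

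**Conclusion.** The concern holds as a point about the rule, without a fixed direction or size of bias. Applied as written, last value carried forward gives no valid estimate of later cost on either reading, and no value for self-reported cost lost before the first survey.

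In the illustration, against a true 3.0 sessions with 10% dropout in each arm, the difference runs from 2.7 to 4.5, with 3.2 for uniform loss carried per period. Unequal loss just after week 4, averaging 10%, gives 1.75 or 7.25 depending on which arm loses more. These figures rest on the session-based assumptions above and show spread, not expected bias. Even where the difference happens to stay at 3.0, the arm totals can be wrong: the running-total case understates each arm by 0.5 sessions. The four-week clinical comparison is not touched by this point. The rule should be amended because cost-effectiveness is part of the primary aim.

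**What to change.** State that carry-forward does not apply to cost data, and replace it with the following:

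1. Count physiotherapy sessions from the treating physiotherapist's survey, with none after recorded discharge. Physiotherapy obtained elsewhere after discharge stays with the participant-reported costs.
2. Impute missing out-of-pocket costs by multiple imputation within arm, period by period, so that each period is filled at its own level. Costs in the other periods, baseline score and site are available as predictors.
3. Report a complete-case cost difference as a sensitivity analysis.
4. State whether the first participant survey covers weeks 0 to 4.

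This needs no new data or visits. The cost is a change of wording, modest extra analysis and a somewhat wider interval for the cost difference, which reflects the information that is missing.

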### Statistical analysis

Data analysis will be undertaken at the completion of data acquisition and will be by intention to treat (that is, participants will be analysed according to group allocation regardless of compliance) [60]. Missing data will be replaced by the last known value carried forward. The statistician will be given coded data to ensure blinding.

Separate analyses will be performed on the four, 12 and 24 week data, with the four-week (i.e., the end of the intervention period) follow-up being the primary time point for analysis. To test the effects of treatment, between-group differences will be examined with analysis of covariance using a regression approach. The emphasis will be on estimation, but hypothesis tests will also be conducted (alpha = 0.05). Pre-test scores will be entered into the model as the only covariate.

In a secondary analysis designed to test the influence of fracture severity on treatment effects, additional terms (fracture severity, group by fracture severity interaction) will be entered into the regression model. Fracture severity will be categorised into two levels based on the number of malleoli involved: less severe (unimalleolar fractures) and more severe (bimalleolar or trimalleolar fractures). The effect of fracture severity on treatment will be determined by examining the interactions between group of allocation and fracture severity.

Ninety participants (45 per group) will participate in the trial. This sample size provides a 90% probability of detecting a difference between group means of 10 points on the Lower Extremity Functional Scale, assuming a standard deviation of 12 based on a recently published study [41]. These calculations assume a correlation of 0.6 between pre- and post-test measures and an alpha of 0.05, and allowed for 10% dropouts and 20% non-compliance.

The economic evaluation will consist of cost-effectiveness and cost-utility analyses. The cost-effectiveness analysis will use the Lower Extremity Functional Scale as a measure of effectiveness. The cost-utility analysis will use the Assessment of Quality of Life as a measure of utility [43]. The analyses will examine differences between treatment and control participants in terms of costs incurred and reductions in perceived disability (cost-effectiveness analysis) or utility gained (cost-utility analysis).

The incremental cost-effectiveness (utility) ratio (ICER) will be calculated as: ICER = (C_E _- C_C_)/(U_E _- U_C_), where C is average cost, U is the average effectiveness or utility score, and subscripts E and C denote the treatment and control arms. Joint mobilisation can be said to be cost-effective relative to exercise alone if it produces less perceived disability and/or greater utility at a lower cost, or the cost per disability avoided or per quality of life gained (i.e., the ICER) is less than some threshold value (e.g., $50,000 in Australian dollars). Sensitivity analysis will be undertaken to explore the robustness and validity of the results. That is, both costs and outcomes will be varied in line with results from similar studies reported in the literature and the upper and lower bounds of the results from this trial.

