**Methods/Design:**

Ninety participants will be recruited from the physiotherapy departments of three teaching hospitals and randomly allocated to treatment or control groups using a concealed procedure. All participants will perform an exercise programme. Participants in the treatment group will also receive joint mobilisation twice a week for four weeks. Blinded follow-up assessments will be conducted four, 12 and 24 weeks after randomisation. The primary outcome measures will be the Lower Extremity Functional Scale and the Assessment of Quality of Life. Secondary outcomes will include measures of impairments, activity limitation and participation. Data on the use of physiotherapy services and participants' out-of-pocket costs will be collected for the cost-effective and cost-utility analyses. To test the effects of treatment, between-group differences will be examined with analysis of covariance using a regression approach. The primary conclusions will be based on the four-week follow-up data.

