## Methods

### Design

This will be an assessor-blinded, multi-centre, randomised controlled trial (Figure 1). Participants will be stratified by site and randomly allocated in permuted blocks to treatment or control groups. The randomisation sequence will be generated a priori using the random number function in Excel by an independent investigator not directly involved in the assessment and treatment of participants. Allocations will be sealed in opaque and consecutively numbered envelopes, which will be opened in sequence by the treating physiotherapist after the recruitment and baseline assessment of each participant.

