### Participants

Participants will be recruited following cast removal from the plaster clinics and physiotherapy departments of three large teaching hospitals in Sydney, Australia (Royal North Shore Hospital, Royal Prince Alfred Hospital, and St Vincent's Public Hospital). The inclusion criteria will be:

• ankle fracture treated with cast immobilisation with or without surgical fixation

• cast removed in the preceding seven days

• approval from the orthopaedic specialist to weight-bear as tolerated or partial weight-bear

• referral to outpatient physiotherapy for treatment

• at least 2 out of 10 pain in the ankle when up to 50% of body weight is borne through the affected leg

• completed skeletal growth assessed by the union of epiphyses on radiographs

• no concurrent and significant injuries or pathologies which may affect the recovery of the participant's lower limb function, and

• available for the six month follow-up period.

In addition to recruiting from multiple sites, other strategies will be used to maximise recruitment rates [40]. A log will be designed to aid the screening of potential participants at each site, and will be monitored by the investigators. Posters about the trial, inservices and regular communication with the participating physiotherapy departments will also assist to facilitate recruitment rates.

Ethical approval will be obtained from the ethics committee of each participating site (i.e., the University of Sydney Human Research Ethics Committee, Northern Sydney Health Human Research Ethics Committee, Sydney South West Area Health Service Ethics Review Committee (RPAH zone), and the St Vincent's Hospital Human Research Ethics Committee).

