### Outcome assessment

Participants will be assessed at baseline and the four, 12, and 24 week follow-up sessions by an assessor blinded to group allocation. The physiotherapists, participants and investigators will be asked to avoid giving information which may reveal group allocation to the blinded assessor. Assessor blinding will be checked after each follow-up assessment. The assessor will be asked if he/she was unblinded and will guess the allocation of each participant.

Demographic information will be collected and an X-ray assessment will be carried out by the blinded assessor at the baseline assessment. The X-ray assessment will determine the angle at which the fractured ankle was immobilised and the number of malleoli involved, in order to investigate the relationships between the angle of immobilisation and fracture severity with outcome.

The primary outcomes will be activity limitation and quality of life. They will be measured by the Lower Extremity Functional Scale [42] and the Assessment of Quality of Life scale [43], respectively. On the Lower Extremity Functional Scale, participants will rate the difficulty they have in performing 20 activities on a five-point scale from zero (extreme difficulty or unable to perform activity) to four (no difficulty). The maximum score is 80 points and a higher score denotes less limitation in activity. When tested in a sample of participants with lower limb injuries that included ankle fracture, the scale showed high internal consistency (alpha = 0.96) and test-retest reliability (intraclass correlation coefficient = 0.86), and correlated well with the physical component of the Short Form 36 [42]. The Lower Extremity Functional Scale is capable of discriminating between patients requiring walking aides and patients not requiring walking aides, and has moderate correlations with weight-bearing status and ankle movement [44].

The Assessment of Quality of Life is designed to measure health-related quality of life, and has 15 questions covering five dimensions: illness, independent living, social relationships, physical senses and psychological wellbeing [43]. It has high internal consistency (alpha = 0.81) [43]. The Assessment of Quality of Life is sensitive to changes in health states and is highly correlated with other commonly-used quality of life scales [46]. Population norms have been calculated for the Australian population [46].

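### Carrying the last value forward at the week-4 primary time point enters the pre-treatment baseline as the outcome, so anyone missing then is scored as not having recovered at all

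*Protocol article*

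**What the plan says.** Under Statistical analysis the protocol article gives one rule for incomplete data, without exception: "Missing data will be replaced by the last known value carried forward". The same section plans separate analyses at 4, 12 and 24 weeks, "with the four-week (i.e., the end of the intervention period) follow-up being the primary time point for analysis", and the abstract adds that "The primary conclusions will be based on the four-week follow-up data". The model is ANCOVA with the pre-test score as sole covariate.

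Under Outcome assessment, "Participants will be assessed at baseline and the four, 12, and 24 week follow-up sessions by an assessor blinded to group allocation", and "The primary outcomes will be activity limitation and quality of life", measured by the Lower Extremity Functional Scale (LEFS, maximum 80) and the Assessment of Quality of Life.

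Two further statements fix what the baseline value represents. Under Design, the allocation envelopes are "opened in sequence by the treating physiotherapist after the recruitment and baseline assessment of each participant". Under Participants, eligibility requires "cast removed in the preceding seven days".

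Missing data are expected: the sample size "allowed for 10% dropouts and 20% non-compliance".

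**The concern.** Nothing is measured on the primary outcomes between baseline and week 4. For a participant without a week-4 score, the last known value can only be the baseline, taken before allocation and soon after the cast came off. The rule therefore imputes a change of exactly zero in people who are expected to be regaining function. It does so even for someone who misses only the week-4 visit and attends at week 12, because later scores play no part in the week-4 analysis. The imputed outcome also equals that person's covariate, and the model treats it as an observation.

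At stake is the primary estimate. Each missing person pulls the arm mean down by the whole of that arm's recovery. With equal losses the treatment effect is diluted and the residual variance rises. With unequal losses the difference in dropout is converted into an apparent treatment difference. The arms differ in visit burden (eight sessions against five) and participants are not blinded, so unequal loss is plausible, though the protocol does not predict it.

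**Working it through.** **The plan's own figure.** Inputs from Statistical analysis: difference 10, SD 12, correlation 0.6, alpha 0.05 (two-sided assumed), power 90%, 10% dropout, 20% non-compliance. With n = 2(1.960 + 1.282)² SD²/10² per arm:

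- Change-score SD 12√(2 × 0.4) = 10.73: n = 25. Dividing by 0.8² for the diluted effect and 0.9 for dropout gives 44 (46 using the t distribution).
- Raw SD 12: n = 31. Dividing by 0.9 × 0.8 gives 44 (45 using t).
- ANCOVA SD 12√(1 − 0.36) = 9.6: n = 20, or 35 after both allowances (37 using t).

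So 45 per group is reproduced to within a patient or so and exceeds what the planned ANCOVA needs. The sample size is not in dispute, but its dropout allowance treats missing people only as lost numbers.

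**Assumptions.** Let R be mean control-arm recovery from baseline to week 4, E the true effect, and p_T and p_C the proportions missing at week 4 in the treatment and control arms. The protocol gives none of R, p_T or p_C. I take R from 5 to 30 LEFS points, data missing completely at random, and no cap at 80.

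**Expected estimate.** A missing person contributes zero change, so

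estimate = (1 − p_T)(R + E) − (1 − p_C)R = (1 − p_T)E − (p_T − p_C)R.

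- 10%/10%: 0.9E, so 10 becomes 9.0 and 8 becomes 7.2, whatever R is.
- 15% treatment, 5% control, E = 10: 8.5 − 0.1R, from 8.0 (R = 5) to 5.5 (R = 30).
- 5% treatment, 15% control, E = 10: 9.5 + 0.1R, from 10.0 to 12.5.
- Either imbalance with E = 0: a spurious difference of 0.1R, from 0.5 to 3.0.

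**Residual variance with 10% missing per arm.** The pooled slope is 0.9 × 0.6 + 0.1 × 1 = 0.64. For an arm with mean recovery M, the variance is 0.9[9.6² + 0.04² × 144] + 0.1 × 0.36² × 144 + 0.09M² = 85.0 + 0.09M². Example for R = 20, E = 8: control 121.0 (M = 20), treatment 155.6 (M = 28), SE = √((121.0 + 155.6)/45) = 2.48, ratio 7.2/2.48 = 2.90, power about Φ(2.90 − 1.96) = 0.83. Simulation of the t-based ANCOVA gives 0.81.

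**Simulated power, true effect 8 (10 diluted by 20%), 45 per arm:**

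| R | 10% missing per arm, carry-forward | ANCOVA on observed data |
|---|---|---|
| 5 | 0.94 | 0.96 |
| 10 | 0.91 | 0.96 |
| 15 | 0.86 | 0.96 |
| 20 | 0.81 | 0.96 |
| 30 | 0.68 | 0.96 |

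With only 5% missing per arm at week 4, carry-forward gives about 0.94, 0.93, 0.90 and 0.83 at R = 10, 15, 20 and 30.

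**Type I error, 15%/5% imbalance in either direction, E = 0:** about 0.06, 0.08, 0.13 and 0.19 at R = 5, 10, 20 and 30 in 20,000 simulated trials per case. With fewer runs the same model scatters between 0.05 and 0.21 across this range. ANCOVA on observed data stays at about 0.05.

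**The case against.** Much of the case on the other side concerns size, and most of that stands.

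- **Power.** A reader might infer that the stated 90% power is not delivered. The documents do not support this as a flat statement: at recoveries of 5 to 10 points power stays above 90%, and it does so at 15 points if only 5% are missing at week 4. The 10% allowance carries no time point and follow-up runs to 24 weeks, so less than 10% may be missing at week 4.
- **Imbalance.** The 15%/5% split is illustrative. Under equal 10% loss the harm is about one point in ten, and interval coverage stays at roughly 92% to 95%.
- **Scale limit.** At R = 30 with an assumed baseline mean of 30, the treated mean would be 70 and about 20% of simulated treated scores would exceed 80. That end of the range should be read loosely. Capping does not rescue the rule; it lowers power there slightly.
- **Costs.** A reader might extend the rule to the four-weekly cost surveys. The protocol does not say it applies to them. The surveys start only at the end of the intervention, and the treating physiotherapists also record sessions.
- **Scope.** The point is sharpest at week 4, because at weeks 12 and 24 the value carried may be post-treatment. Satisfaction and global perceived effect have no baseline to carry.

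It might also be said that an analysis plan not shown here could settle missing data. That does not meet the point: the protocol does not leave the method open but names one, and the only sensitivity analysis it describes belongs to the economic evaluation.

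**Conclusion.** The rule is wrong as written for the primary analysis. That follows from the rule, the visit schedule and the primary time point alone, and needs no outside figure. It holds for both primary outcomes, although the size can be worked out only for the LEFS, since the protocol gives no SD for the quality-of-life scale.

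The magnitude is conditional on SD 12, correlation 0.6, 45 per arm, data missing completely at random, recovery of 5 to 30 points and no cap at 80. Equal 10% loss costs about 10% of the effect. Power for the diluted effect may fall below 90% if recovery exceeds roughly 10 points and the full 10% are missing at week 4. Unequal loss biases the estimate against the arm that loses more people. At 15%/5% the bias on a true 10 runs from about −2.0 to −4.5 points, or from about 0 to +2.5 if reversed, and the type I error runs from close to nominal to nearly 20%. The rule therefore cannot be defended as safely conservative, nor can it be said in advance to favour one arm.

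**What to change.** Replace the carry-forward sentence. Either of these serves as the primary week-4 analysis:

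- a likelihood-based repeated-measures model on all observed 4-, 12- and 24-week scores, with baseline score, group, visit and group-by-visit, reading the treatment effect at week 4; or
- the planned ANCOVA after multiple imputation by arm, using baseline and later visits. This keeps the stated single-covariate model.

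Keep carry-forward at most as a sensitivity analysis, and add one missing-not-at-random (delta) analysis. ANCOVA on observed data would already remove the bias if data were missing completely at random. The two options above also use the later scores of those who return, and they need only the weaker missing-at-random assumption.

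The cost is a change of analysis wording and a little more programming, with no new data. The price is reliance on missing at random, which the delta analysis is there to probe. Nothing here requires a change to the sample size or the addition of site to the model.
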